# **A Randomised Controlled Trial of the “Take a Breath” Parent Program: Evaluation of A Program to Reduce Distress in Parents of Children with Serious Childhood Illnesses/injuries**

## **2. INTRODUCTION AND BACKGROUND**

### **2.1 Background Information**

It has been well established that serious child illness or injury's (SCII) which are life threatening and have long term consequences for child wellbeing, have significant impacts on child health and development, including social, educational, physical and emotional domains. Importantly, these increased problems occur not just for the sick child (Caplan et al., 2005; Hudson et al., 2003; Zebrack et al., 2002) but also for parents, and for mothers in particular (Pai et al., 2007; Pai et al., 2008). Parents of a child with an SCII must, for example, contend with the possibility of their child's death along with the serious impact on their child's future (Hall et al., 2006). These experiences can overwhelm even the most resilient parents (Hall et al., 2006).

Research findings from studies exploring the impact of SCII have indicated that most families of a child with SCII are able to cope and adjust well over time despite initial and/or recurrent periods of extreme distress (A. Kazak et al., 2007; Landolt, Vollrath, Ribi, Gnehm, & Sennhauser, 2003; Tyack & Ziviani, 2003). However, it has also been documented that for some families, family functioning will be adversely affected by elevated or escalating psychological distress in parents (Chesire, Barlow, & Powell, 2010; Mu, 2005; Shaw et al., 2006; Williams et al., 2003). Similar to other traumatic experiences, the experience of having a child diagnosed with a SCII can lead to parental depression, acute stress disorders and/or post traumatic stress responses (Best, Streisand, Catania, & Kazak, 2001; Chesire et al., 2010; Cleveland, 2008; A. Kazak & Barakat, 1997). This link between parental mental health and SCII has been seen across a range of diagnoses including: cancer, acquired brain injury and admission to Intensive Care Units (Sawyer, Streiner, Antoniou, Toogood, & Rice, 1998).

Research suggests that the early months of treatment provide an important window to intervene to reduce short and longer-term post traumatic symptoms in parents (A. Kazak et al., 2007). Some attention has been given to the investigation of approaches for supporting parents of children with SCII and in particular childhood cancer. Many of these approaches have targeted parents with existing symptoms of trauma and distress. Results of studies have been mixed. While some studies have demonstrated significant impacts on parental coping and wellbeing (A Kazak et al., 1999; O. Sahler et al., 2002), other studies have reported interventions to be less effective than required to support wide dissemination. Two studies aimed at reducing parental symptoms of traumatic stress in parents of children with cancer have demonstrated some success. The first, the Surviving Cancer Competently Intervention Program (SCCIP: (A Kazak et al., 1999) is a one day group cognitive behavioural and family systems intervention whilst the second is a problem solving skills training program, (PSST: (O. Sahler et al., 2002) delivered on an individual basis to parents over eight

43 sessions. Findings from families participating in either the SCCIP or PSST interventions  
44 revealed both programs were effective in reducing maternal emotional distress and anxiety  
45 associated with the diagnoses of life-threatening illnesses. However, both these  
46 interventions report some problems, with the SCCIP reporting difficulties with engagement  
47 of parents and the outcomes from the PSST program diminishing at three month follow-up  
48 assessment. Another study, evaluated the effectiveness of a parent component of the four  
49 session Children's Epilepsy Program (Lewis, Hatton, Salas, Leake, & Chiofalo, 1991). The  
50 parent component was designed to help parents acknowledge their fears, grief, and anger  
51 surrounding their child's seizure disorder, as well as to have a better understanding of the  
52 disorder (Lewis et al., 1991). The results from the pilot study revealed gains in parental  
53 knowledge and reductions in anxiety, but did not result in changes to parental vigilance and  
54 the restrictions they placed upon their child's self-care activities or how they controlled their  
55 seizures, a major aim of the intervention (Lewis et al., 1991). The sparse amount of  
56 intervention research to date and the mixed results of the few published studies highlight  
57 the need for further investigation and development of effective interventions that prevent  
58 traumatic stress symptoms in parents from reaching clinical levels.

59 More recently psychosocial interventions are moving into online platforms to enhance  
60 the feasibility of research studies, and to provide rural and regional families access to  
61 potentially useful programs. Large tertiary paediatric hospitals like Melbourne's RCH receive  
62 admissions from across the state as well as from interstate and overseas. Our longitudinal  
63 study of 194 parents of children with SCIs found 46% lived in regional, rural or interstate  
64 areas. To ensure equity of access the use of an online videoconferencing is a viable option.  
65 The efficacy of telepsychiatry and other technology-assisted psychological interventions  
66 services has been studied for over 15 years. While the number of quality RCTs remains small,  
67 the evidence consistently supports these approaches as having effect sizes equal to and  
68 sometimes stronger than traditional face-to-face intervention. Meta-analyses of technology-  
69 assisted interventions for the treatment of adult anxiety, depression, or trauma span  
70 interventions delivered individually or in groups, using on-line text-based intervention, tele-  
71 and videoconferencing for groups or individuals, and self-help programs with or without  
72 therapist assistance (Barak, Hen, Boniel-Nissim, & Shapira, 2008). There is also growing  
73 evidence that elements of the therapeutic alliance (which arguably account for a substantial  
74 proportion of outcomes irrespective of the intervention components),(Frueh et al., 2007)  
75 remain similar regardless of mode of delivery (Cook & Doyle, 2002; Frueh et al., 2007). For  
76 example, Frueh et al (2007) evaluated a manualised intervention for PTSD (N=38) and found  
77 no differences by modality (group teleconferencing) in terms of therapist competence,  
78 adherence, providing feedback, developing rapport, managing difficulties and conveying  
79 empathy.

### 81 **2.3 Rationale for Current Study**

82 The newly developed Take a Breath (TAB) parent program, which targets parents at risk  
83 for developing serious psychosocial difficulties, offers an important opportunity to provide  
84 tailored support to families with the potential to prevent ongoing difficulties and to assist  
85 families to adapt well to the new and often overwhelming experience of having a seriously ill  
86 child. The program incorporates key strategies that have demonstrated promise in previous  
87 intervention trials for parents of children with an SCI whilst adding additional therapeutic  
88 elements that have demonstrated good effect in other areas of psychological trauma and  
89 distress. It is anticipated that the combination of these therapeutic elements will lead to

prevention of ongoing and severe levels of traumatic stress in vulnerable parents of children with a range of serious childhood illnesses.

### **3. STUDY OBJECTIVES**

#### **3.1 Primary Objective**

Does the “Take A Breath program lead to greater improvements in psychosocial distress than treatment as usual for parents of children with SCIs who report risk factors associated with the development of post traumatic stress symptoms in the first weeks following their child’s diagnosis.

### **4. STUDY DESIGN**

#### **4.1 Type of Study**

The design is a pre-post- control group design with random allocation to one of two treatment arms:

- TAB (Take a Breath) parent intervention
- Wait List control (W-L).

This design will allow a comparison of the TAB and wait-list groups at pre and post intervention, in order to evaluate if any improvements over time are due to the TAB intervention and not due to natural recovery or other factors. Following completion of the post questionnaire, the W-L group will be offered the TAB intervention if they are interested, to acknowledge their time commitment and participation in the project. If they do complete the group, they will also be asked to complete a post-intervention questionnaire.

Up to 30 parent groups will be delivered per arm across a two and a half year period commencing in November 2014. Parents assigned to the TAB arm will be offered a place in the next available parent group. Parents assigned to the W-L arm will be offered participation in the TAB program immediately after completion of the post intervention questionnaire.

#### **4.3 Number of Subjects**

##### Screening of Parents: Identifying Target Participants

Up to 788 parents will participate in the Screening process in order to reach the targeted group. It is anticipated that this number of parents will be required to reach the 263 eligible and consenting parents that are required for adequate power for the parent intervention analysis. This figure was arrived at by allowing for a seventy percent uptake at screening, a 5% drop due to child death/grave illness and 50% excluded as reporting no distress.

It is considered that this figure of 788 is feasible based on the number of past admissions from each of the three participating departments in a 12 month period. For example, during 2008-2009 there were approximately 200 new cancer, 1600 Cardiac, and there were approximately 1000 admissions to the PICU. Given these figures and the research experience of the research team, it was estimated that approximately 70% of families admitted into the hospital in each of the illness/injury groups would be likely to participate resulting in

sufficient numbers of families willing to complete the screening questionnaire. See figure 3 below outlining recruitment, assessment and participant flow.

### Parent Intervention Participants

One hundred and eighty four families will be allocated to each of the two treatment arms. A potential total of 263 eligible parents are required, as we anticipate that 50% of eligible families will either be uncontactable, refuse to participate, or their child's illness will exclude them from participating at this later stage. See Figure 3 for participant flow details.

[figure not shown]

Figure 1: Recruitment, assessment & participant flow

Figure 3: Recruitment, assessment and participant flow

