#### Randomisation Procedures

Eligible parents will be randomised to either the parent intervention group or the W-L group. This will typically occur between three and four months post their child's diagnosis.

Three randomisation lists will be generated, one list per participating department. This will enable separate analysis by illness group as well as an overall exploration of outcomes for families of children with SCII. Each randomisation list will contain twenty six spaces. Participants will be randomly allocated to one of the two treatment arms using The RCH Department, Clinical Epidemiology and Biostatistics Unit (CEBU), computerised randomisation plan generator. This program will randomise each participant to one of the two treatment arms using the method of randomly permuted blocks. The end result will be two randomly allocated treatment arms of equal size divided between three randomisation lists organised according to Hospital Department (Cancer, Cardiac and PICU).

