## **7.6 Trial Closure**

Once the designated number of participants in the study has been reached (e.g., 184 participants have been randomised the RT will inform The RCH departmental staff who have been promoting the study, that the study is closed to new participants. If potential participants contact the RT to participate, they will be provided with appropriate alternative referral options if needed. As outlined in the PDCF, participants will be provided with a summary of group outcomes of the study. It is not anticipated that the study will cease prematurely. The only foreseeable circumstance would be if funding for the study was withdrawn. However in this case the RT would seek additional funding to complete the study. Should any difficulties arise with recruiting the required number of participants, an extension to continue the study will be sought. Again additional funding will be sought to extend the study to ensure that the adequate number of participants has been achieved to complete the study.

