### **8.2 Parent Intervention Groups**

A total of 263 parents will participate in the main RCT study. It is anticipated that up to 30 parent groups will be delivered. A maximum of 10 parents will be enrolled into each group to ensure that parents can participate fully in all aspects of the program.

Parent groups will be scheduled on different days and times, with evenings and/or weekends being available. Sessions will be held once per week for a total of five consecutive weeks with a sixth session held two to four weeks later. The sixth session is included as it provides parents with a short period to practice and implement the skills and ideas taught during the program and to address any difficulties or barriers that arise when implementing them. All sessions will be delivered via online videoconferencing using Google Hangouts.

Parent programs will be commenced when enough parents have been randomised to the TAB treatment arm to constitute a group (a minimum of 5). Parents randomised to the Wait List arm will receive their pre questionnaires at the same time as the parents scheduled to commence that TAB group. In this way the timing for their assessment points will be matched to the participants in the TAB treatment arm.

Parents will be monitored by the practitioner facilitating the group they are attending throughout the intervention and at each assessment point. Evaluation questionnaires will be used to support the clinical judgment of the practitioner.

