## **11. STATISTICAL METHODS**

### **Sample Size Estimation**

In order to detect a difference of 6.0 (SD: 13.9) points (thought to be a clinically important difference in parents' experience of distress) in the Posttraumatic Stress Disorder Checklist (PCL- 5) measure, between the two treatment arms, with a significance level of 0.05 and power of 0.80, 82 participants will be required per arm. Allowing attrition, we therefore aim to recruit a total of 184

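### The sample size of 184 randomised in total is contradicted by 184 per arm, by 263 in the RCT and by lists of 78 places, and the stated 50% loss leaves only about 131 parents

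*Protocol*

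**What the plan says.** The protocol gives the size of the randomised comparison in several places.

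- **Section 11, Sample Size Estimation.** The basis is "In order to detect a difference of 6.0 (SD: 13.9) points" on the PCL-5, "with a significance level of 0.05 and power of 0.80, 82 participants will be required per arm". The section then states: "Allowing attrition, we therefore aim to recruit a total of 184".
- **Section 7.6, Trial Closure.** Recruitment closes at the same total ("184 participants have been randomised the RT will inform" departmental staff). The section adds that an extension and further funding will be sought if recruitment is difficult.
- **Section 4.3, Parent Intervention Participants.** "One hundred and eighty four families will be allocated to each of the two treatment arms". The next sentence reads: "A potential total of 263 eligible parents are required, as we anticipate that 50% of eligible families will either be uncontactable"; refusal and the child's illness are the other reasons given for the loss.
- **Section 4.3, Screening of Parents.** Up to 788 parents are screened to reach 263. Here the 263 are described as already eligible and consenting, and as the number needed for adequate power. The stated steps are 70% uptake, a 5% loss through death or grave illness of the child, and 50% excluded for no distress. Section 8.1 calls 788 a maximum.
- **Section 8.2, Parent Intervention Groups.** "A total of 263 parents will participate in the main RCT study".
- **Randomisation Procedures.** There are three lists, one per department: "Each randomisation list will contain twenty six spaces".

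**The concern.** These statements cannot all be followed. The same figure, 263, is a pool before refusals in one paragraph, a consenting sample in another and the number taking part in the RCT in a third. The figure 184 is a total in two sections and a per-arm number in a third. The list length fits none of these totals.

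Separately, the recruitment forecast, worked through with its own percentages, does not produce the 184 at which the trial is to close.

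The number randomised governs when recruitment stops, how many parents must be approached, how long the allocation lists must be and what power can be claimed. Staff working from sections 4.3, 7.6 and 8.2 would aim at 368, 184 and 263 respectively. With several targets on record, different achieved sizes could each be reported as the planned one.

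**Working it through.** **1. The plan's own calculation (section 11).** Inputs: difference 6.0, SD 13.9, significance level 0.05 (sidedness not stated, two-sided assumed), power 0.80, equal arms.

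n per arm = 2 × (1.96 + 0.842)² × 13.9² / 6.0² = 84.3, so 85. The t-test solution is 85.2, so 86. The stated 82 is slightly low: with 82 per arm the power is 78% (t-test) to 79% (normal approximation). This is a small miss and nothing below depends on it.

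The total follows from it: 2 × 82 = 164 analysed. Recruiting 184 implies attrition of 1 − 164/184 = 10.9%, a rate the protocol does not state. So 82 per arm and 184 in total fit together.

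**2. Section 4.3 against itself.** 2 × 184 = 368 allocated, from 263 eligible. That is 140% of the pool (368/263 = 1.40) before any loss. The sentence counts families; counting couples as one family would only widen the gap.

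**3. The recruitment forecast.**

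- Screening: 788 × 0.70 × 0.95 × 0.50 = 262. The 263 is therefore the pool before the later loss, not a consenting or randomised sample.
- Later loss as stated: 263 × 0.50 = 131.5, about 131 randomised. This is below 184 and below the 164 needed for analysis.
- Loss rate that would give 184: 184/263 = 0.70, a 30% loss (263 × 0.70 = 184.1).
- Pool needed if 50% is right: 184/0.50 = 368 eligible, and 368/(0.70 × 0.95 × 0.50) = 368/0.3325 = 1,107 approached, against the maximum of 788.

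**4. Randomisation lists.** 3 × 26 = 78 places. If the spaces are per arm, 2 × 78 = 156. Both are below 184, so at least one list must be exhausted by the 79th allocation (or the 157th on the per-arm reading).

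**5. Power at each total** (two-sample t-test, two-sided 0.05, d = 6.0/13.9 = 0.432, equal arms):

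| Total randomised | Source | No attrition | 10.9% attrition |
|---|---|---|---|
| 131 | 263 with 50% loss | 69% | 64% |
| 184 | sections 11 and 7.6 | 83% | 78% |
| 263 | section 8.2 | 94% | 91% |
| 368 | section 4.3, per arm | 98.5% | 97% |

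Clustering within couples and within parent groups is ignored, as in the plan's own calculation.

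**The case against.** The strongest reply is that the governing number can be recovered. Section 11 derives 184 in total and section 7.6 closes the trial at 184. On that view, the words *to each* in section 4.3 and the 263 in section 8.2 are slips, and computer-generated lists can be extended. Much of this stands, and it rules out three stronger readings.

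- A reader might infer that the 80% power has no consistent sample size behind it. The documents do not support that: sections 11 and 7.6 agree, and 184 gives 78–79% power after the implied attrition.
- A reader might infer that the trial is planned at 64% or 69% power, or at 47% if allocation stopped at 78. These figures are conditional. Section 7.6 ties closure to 184 and foresees an extension, so a shortfall would first mean longer recruitment. The 47% also requires that no list is ever extended.
- A reader might infer that every list runs out before half the sample is allocated. That would need each department to supply at least 26 of the first 92 parents (28%), and the protocol gives no department shares of randomised parents. Only the exhaustion of at least one list is certain.

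The reply does not remove the error. Correcting *to each* leaves the 50% loss against a pool of 263, a stated screening maximum of 788, the two other uses of 263, and lists too short on either reading. The participant flow figure was not available, but no figure can fit 368 into 263 or make half of 263 equal 184.

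**Conclusion.** The point holds in this form: one coherent size, 184 randomised in total, underlies the power statement. Section 4.3 (in both its parts), section 8.2 and the Randomisation Procedures contradict it, and the recruitment forecast does not reach it.

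The size of the conflict is 368 or 263 against 184 for the number in the trial, 78 (at most 156) against 184 for list places, and about 131 against 184 for the expected yield. If recruitment ended at the stated screening maximum, the expected yield would also fall short of the 164 needed for analysis by about 33 parents even with no attrition, with power of about 69% (64% with attrition).

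The contradictions and the yield rest only on stated figures. The power values assume a two-sided test, and the lower one also assumes the 10.9% attrition inferred from 164/184. This should be corrected before the protocol is relied on, because closure, screening and allocation all use the number.

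**What to change.** 1. In section 4.3, Parent Intervention Participants, state 184 parents randomised in total, 92 per arm.
2. In section 4.3, Screening of Parents, and in section 8.2, describe the 263 as eligible parents to be invited. They are neither consenting parents nor RCT participants, and the number required for power is that of section 11.
3. Reconcile the later loss with the pool. If 30% was the assumption that took 263 to 184, replace the 50%. The 30% is inferred from 184/263 and stands nowhere in the protocol, so the sponsor must confirm it. If 50% is right, keep it and say that 263 eligible parents are expected to yield about 131 randomised, with the matching power (69% before attrition, 64% after). Say also that reaching 184 needs 368 eligible parents, about 1,107 approached, and revise the maximum of 788 in sections 4.3 and 8.1 if 184 is to be met.
4. Say whether a space is one allocation or one per arm, and generate the three department lists long enough for 184 allocations whatever the department shares turn out to be.

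The cost is protocol wording and longer computer-generated lists. If the 50% is kept, either the screening target rises or a less favourable expected power is put on record.

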## 5. STUDY TREATMENTS

### 5.1 Treatment Arms

#### 5.1.1 Description

##### Program Structure

The parent intervention is a brief psychosocial parent mediated group program. It will consist of five sessions of 90 minutes duration each plus one additional sixth session (also 90 minutes) one month following the fifth session (totalling nine hours of contact time). The intervention will be delivered via an online videoconferencing platform called Google Hangouts <https://hangouts.google.com/> supported by the Royal Children's Hospital. This

program allows participants and practitioner/s to see and hear each other, including the option of presenting teaching materials on the screen. Participants are also able to send group emails and private emails to the practitioner if they chose to do so. Each participant will be sent an I-pad (set up for immediate use) for the duration of the program, programmed with Google hangouts, and specific instructions on how to login to the session. The I-pad will have internet access, with ample download capacity with Telstra to prevent disruption throughout this period. Internet access will be restricted to the Google hangouts application, limiting extraneous use of the internet. This process will ensure all participants have access to the technology and will minimise technical issues.

Voice recordings will be taken in each group, and used to assess program fidelity. To maintain privacy, participants will be requested to enter their first name only, which will be visible underneath their webcam image. An overview of the program's structure and content is provided in Appendix 11: TAB Program Outline.

